**\*\*R6 will be prevented by very careful established security guidelines.**

#### 10.1.2 Definition and Assessment of (Serious) Adverse Events and other safety related events

##### Definitions:

##### - Adverse Event (AE)

Any untoward medical occurrence, unintended disease or injury or any untoward clinical signs (including an abnormal laboratory finding) in participants, users or other persons whether or not related to the investigational medical device [ISO 14155: 3.2].

NOTE 1 This definition includes events related to the investigational medical device or the comparator.

NOTE 2 This definition includes events related to the procedures involved.

NOTE 3 For users or other persons, this definition is restricted to events related to investigational medical devices.

##### - Adverse Device Effect (ADE)

Adverse event related to the use of an investigational medical device [ISO 14155: 3.1].

NOTE 1 This definition includes adverse events resulting from insufficient or inadequate instructions for use, deployment, implantation, installation, or operation, or any malfunction of the investigational medical device.

NOTE 2 This definition includes any event resulting from use error or from intentional misuse of the investigational medical device.

##### - Serious Adverse Event (SAE) [ISO 14155: 3.37]:

Any adverse event that led to any of the following:

- (a) death,
- (b) serious deterioration in the health of the subject that resulted in any of the following:
  - (i) life-threatening illness or injury,
  - (ii) permanent impairment of a body structure or a body function,
  - (iii) hospitalisation or prolongation of patient hospitalisation,
  - (iv) medical or surgical intervention to prevent life-threatening illness or injury or permanent impairment to a body structure or a body function,
- (c) foetal distress, foetal death or a congenital physical or mental impairment or birth defect.

NOTE 1 Planned hospitalization for a pre-existing condition, or a procedure required by the CIP, without serious deterioration in health, is not considered a serious adverse event.

*- Device deficiency:*

Inadequacy of a medical device related to its identity, quality, durability, reliability, safety or performance, such as malfunction, misuse or use error and inadequate labelling [ISO 14155: 3.15].

*- Device deficiency with SAE potential:*

Device deficiencies that might have led to a serious adverse event if a) suitable action had not been taken or b) intervention had not been made or c) if circumstances had been less fortunate.

*- Health hazards that require measures:*

Findings in the trial that may affect the safety of study participants and, which require preventive or corrective measures intended to protect the health and safety of study participants SAE [ClinO Art. 37].

*- Causal Relationship of SAE [MEDDEV 2.7/3 revision 3, May 2015]:*

A causal relationship towards the medical device or study procedure should be rated as follows:

- **Not related:** The relationship to the device or procedures can be excluded.
- **Unlikely:** The relationship with the use of the device seems not relevant and/or the event can be reasonably explained by another cause, but additional information may be obtained.
- **Possible:** The relationship with the use of the investigational device is weak but cannot be ruled out completely. Alternative causes are also possible.
- **Probable:** The relationship with the use of the investigational device seems relevant and/or the event cannot reasonably explained by another cause.
- **Causal relationship:** The serious event is associated with the investigational device or with procedures beyond reasonable doubt.

Device deficiencies that might have led to an SAE are always related to the medical device.

### Assessments:

Any AE, ADE, SAE or Device Deficiency will be analysed and reported carefully during the whole study period. Measures will be taken accordingly (see 10.1.3). At end of study visit (V3) every participant will be interviewed by the study nurse if any additional AE, ADE, SAE or Device Deficiency has occurred not already mentioned up to V3.

Participants are informed that they should report any event immediately to the study nurse by calling or mailing the study nurse. The study nurse will record the report in the CRF and determine if it is a (Serious) Adverse Event, ADE or Device Deficiency.

The study nurse, or other study team member, will report to the PI within 24 hours of the event:

- All SAEs
- Device deficiencies

The Sponsor-Investigator will evaluate SAEs with regard to causality and seriousness. Device deficiencies are assessed regarding their potential to lead to an SAE.

Device deficiencies will also be reported to the Manufacturer (Healios).

In addition, the DREAMS App has a relapse reporting process, see Appendix 17.5.1.5. All relapses reported are captured in the Nurse Portal and will be followed up by the study nurse.

The study team will also ask all study participant for any (Serious) Adverse Events during the End of Study visit (Visit 3).

### **10.1.3 Reporting of (Serious) Adverse Events and other safety related events**

#### Reporting to Sponsor-Investigator:

The following events are to be reported to the Sponsor-Investigator within 24 hours upon becoming aware of the event:

- All SAEs
- Health hazards that require measures
- Device deficiencies

The Sponsor-Investigator will evaluate SAEs with regard to causality and seriousness. Device deficiencies are assessed regarding their potential to lead to an SAE.

#### **Pregnancies**

Pregnancy is one of the exclusion criteria for the study. Participants that become pregnant during the study will need to report this to the study nurse/study physician. The participant will decide to complete the study or to proceed to early termination due to pregnancy.

#### Reporting to Authorities [ClinO Art. 42]:

In Category C studies it is the Investigator's responsibility to report serious adverse events in Switzerland, where it cannot be excluded that the events are attributable to the device under investigation, or to an intervention undertaken in the clinical trial to the Ethics Committee via BASEC within 7 days. The Sponsor-Investigator reports within the same timeline to Swissmedic (incl. events from abroad).

It is the Investigator's responsibility to report device deficiencies to the Ethics Committee via BASEC that could have led to serious adverse events if suitable action had not been taken, intervention had not been made, or circumstances had been less fortunate within 7 days. The Sponsor-Investigator reports within the same timeline to Swissmedic (incl. events from abroad) [ClinO Art. 42].

Health hazards that require measures are reported to Swissmedic and to the Ethics Committee via BASEC within 2 days [ClinO Art. 37]. Periodic safety reporting:

In Category C studies a yearly safety update-report is submitted by the Investigator to the Ethics Committee and by the Sponsor-Investigator to Swissmedic.

#### **10.1.4 Follow up of (Serious) Adverse Events**

The follow-up will be defined by the PI at an individual study participant level.

### **11. STATISTICAL METHODS**

#### **11.1 Hypothesis**

Null Hypothesis: It is not possible to identify reliable, well accepted biomarkers.

Alternative Hypothesis: It is possible to identify at least one reliable, well accepted biomarker for the following domains: a) vision b) cognition c) dexterity d) movement.

#### **11.2 Determination of Sample Size**

Due to the iterative study design, no formal sample size calculation was performed. The sample size of 30 PwMS and 30 HC was estimated based on published results of similar research in the field (Midaglia et al., J Med Internet Res. 2019).

#### **11.3 Statistical criteria of termination of trial**

There are no statistical discontinuation criteria for individual study participants.

#### **11.4 Planned Analyses**

##### **11.4.1 Datasets to be analysed, analysis populations**

All subjects who completed the study will be included in the primary analysis (per protocol analysis). An additional "intention-to-test" analysis comprising all eligible subjects will be performed as a sensitivity analysis.

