## 7.4 Criteria for withdrawal / discontinuation of participants

Patients and healthy controls will be withdrawn from the study if the following occurs during the study period:

- Other clinically significant concomitant disease states (e.g., renal failure, severe hepatic dysfunction, severe/unstable cardiovascular disease, progressive cancer, etc.)
- Non-compliance
- Inability to follow the procedures of the study, e.g. due to language problems, psychological disorders, dementia, etc. of the participant
- Pregnancy: If a participant will realise pregnancy during the study period, she should contact the study nurse. The participant will be allowed to continue the study if she wants to but of course can also withdraw consent immediately.
- Loss of their DREAMS App compatible smartphone (iOS/Android, see section 3.2.4, Table 2)
- Close visual acuity loss of  $< 0.5$
- Loss of hand motor skills not sufficient for using a smartphone
- Using PEAK\* during the study period

\* PEAK: freely available App for cognitive training

Withdrawn participants (drop-out) will be replaced by an additional participant.  
Data of withdrawn participants collected until withdrawal will not be deleted and will be used in a coded form for research purposes.

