### **8.4 Compliance with study intervention**

Study nurse will be alerted if user completes < 75% of exercises (i.e. missing >2) for at least 2 out of 5 days. The study nurse will contact participants by phone if this is the case to offer help. Participants can contact the study nurse and the study physician anytime. Non-compliance (sustained non-adherence to completion of the scheduled exercises) will result in withdrawal. After withdrawal we will try to get withdrawn participants feedback (semi-structured interview) for understanding the reason for non-compliance.

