## **8.6 Data Collection and Follow-up for withdrawn participants**

Data from withdrawn participants (drop out) will be included into analysis (intention to treat analysis). Withdrawn participants will be asked if they would be willing to be invited for the feedback interview in order to learn from their experience with the App. This will take place in study visit V3. The study design has no official follow-up visit.

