| R7              | Instructions              | Instructions are not clear       | Instructions are not clear                                                           | Tests are not executed as intended                                    | Nuisance and impact                    |

|     |                  |                                      |                                                             |                                                                                               |                                        |
|-----|------------------|--------------------------------------|-------------------------------------------------------------|-----------------------------------------------------------------------------------------------|----------------------------------------|
|     |                  |                                      |                                                             |                                                                                               | on study execution                     |
| R8  | Labelling issues | n/a                                  | n/a                                                         | n/a                                                                                           | n/a                                    |
| R9  | IT systems       | App malfunctions                     | Changes or errors in third party and/or open libraries used | -partici-pant is not able to perform activities
- Outcomes may not be presented accurately | Nuisance and impact on study execution |
| R10 | IT Systems       | Interference with other devices/Apps | Interference with other devices/Apps                        | Interference with other devices/Apps                                                          | Bad user experience                    |
| R11 | General          | Biocompatibility issues              | n/a                                                         | n/a                                                                                           | n/a                                    |

Table 11: Potential adverse events DREAMS App. n/a= not applicable

**\*R1 will be prevented by a very careful instruction at BL. If any safety concern exists participant will not be included or will be included but challenge with safety concerns will not have to be performed (can be deleted individually on the schedule by the study nurse).**

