**A mean response of > 3 on a Likert Scale will be the minimal requirement for test selection.**

b) Adherence will be calculated as percentage of completed repetitions divided by the total number of scheduled repetitions for each test. **The minimal adherence required for test selection will be 80%.**

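### The 80% adherence gate is decided in completers, after sustained non-adherers have been withdrawn and replaced, so the deciding adherence figure is biased upward

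*Protocol*

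**What the plan says.** Section 11.4.1 of the protocol sets the population for the primary analysis: "All subjects who completed the study will be included in the primary analysis (per protocol analysis". The synopsis repeats this. The next sentence of 11.4.1 adds an intention-to-test analysis "comprising all eligible subjects will be performed as a sensitivity analysis".

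The primary analysis (11.4.2) selects tests in steps. Step 2 defines adherence: "Adherence will be calculated as percentage of completed repetitions divided by the total number of scheduled repetitions for each test". It then sets the threshold: "The minimal adherence required for test selection will be 80" per cent. It also requires a mean acceptance rating above 3 on a five-step scale. Step 3 ranks only tests that meet both requirements as well as a reliability criterion.

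Section 8.4 states: "Non-compliance (sustained non-adherence to completion of the scheduled exercises) will result in withdrawal". Section 7.4 also lists non-compliance as a reason for withdrawal and states: "Withdrawn participants (drop-out) will be replaced by an additional participant". Section 11.5 repeats the replacement rule. Section 7.4 keeps the data collected up to withdrawal.

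Section 8.6, and 9.2.5 in the same words, state: "Data from withdrawn participants (drop out) will be included into analysis (intention to treat analysis". Under 8.4, 8.6 and 9.2.5, withdrawn participants are invited to a feedback interview. The rated questionnaire is not named for them.

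**The concern.** Adherence to each test is a pass/fail criterion. The people most likely to pull it down are removed for low adherence, replaced by new participants, and then left out of the set in which the criterion is judged. For an outcome such as ICC or CV, restricting to completers can be defended, because reliability needs repeated measurements. For adherence it cannot be defended in the same way, because stopping is part of what is being measured.

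The study's product is the list of tests that go on to validation. If the deciding figure is too high, a test that patients do not keep up can be carried forward as feasible. The planned all-eligible analysis could reveal this, but the protocol does not say that it can change a selection.

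**Working it through.** **Inputs from the protocol.** 30 participants per group (11.2); adherence gate of at least 80%; acceptance gate above 3; ten repetitions per test (6.1). The protocol has no calculation of its own to reproduce here. It gives no drop-out rate and no numerical definition of sustained non-adherence, so every rate below is an assumption.

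**1. Adherence over everyone enrolled.** With 30 completers at rate *c* and *d* withdrawn participants who completed a share *w* of their planned repetitions:

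all-enrolled adherence = (30*c* + *dw*) / (30 + *d*)

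For *c* = 0.85 and *w* = 0.30:

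| Withdrawn | Calculation | All enrolled | Completers |
|---|---|---|---|
| 3 | (25.5 + 0.9)/33 | 80.0%, passes | 85%, passes |
| 4 | (25.5 + 1.2)/34 | 78.5%, fails | 85%, passes |
| 6 | (25.5 + 1.8)/36 | 75.8%, fails | 85%, passes |

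**2. How many withdrawals reverse a pass.** The gate fails once *d* exceeds 30(*c* − 0.80)/(0.80 − *w*).

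- *c* = 0.82, *w* = 0.20: 30 × 0.02/0.60 = 1.0, so 2 withdrawals reverse it.
- *c* = 0.85, *w* = 0.40: 30 × 0.05/0.40 = 3.75, so 4.
- *c* = 0.90, *w* = 0.60: 30 × 0.10/0.20 = 15, so 16.

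**3. Effect of the filter alone.** In a simulation, each person's adherence was drawn from a Beta distribution (precision 5) and ten repetitions were generated. Persons whose underlying adherence lay below a cut-off were withdrawn and replaced until 30 completed (5,000 runs). True mean adherence was 76%, below the gate.

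| Cut-off | Mean number replaced | Completer mean | Chance of passing, all starters | Chance of passing, completers |
|---|---|---|---|---|
| 40% | 1.3 | 77.9% | 16% | 30% |
| 50% | 3.2 | 79.9% | 16% | 52% |
| 60% | 6.8 | 82.6% | 15% | 83% |

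The direction was upward in all nine scenarios run (true mean 74% to 78%, cut-off 40% to 60%). The model takes a person's adherence to the test as equal to the adherence on which withdrawal is decided. Under the protocol, withdrawal depends on the whole schedule, so the effect on any one test would be weaker if adherence to that test differs from adherence overall.

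**4. Acceptance.** The same weighted mean applies. With completers at 3.2, withdrawn participants at 2.0 and 6 withdrawn: (30 × 3.2 + 6 × 2.0)/36 = 108/36 = 3.00, which fails a gate of more than 3. If withdrawn participants rate as completers do, the mean does not move.

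**5. Challenges removed from a schedule.** Section 10.1.1 (note to R1) allows that a "challenge with safety concerns will not have to be performed (can be deleted individually on the schedule by the study nurse". Suppose this applies to 5 of 30 participants and the other 25 do 90%. If scheduled means each person's edited schedule, the test scores 90%. If it means the common schedule in Table 5, it scores 25 × 0.90/30 = 75%. The protocol does not say which is meant.

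**The case against.** The strongest reply is that 11.4.1 already plans an analysis of all eligible subjects, so nothing is hidden. That is correct, and a reader should not infer that completers are the only set analysed. But it is a sensitivity analysis with no stated consequence, so completers decide selection.

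A reader might also infer that the gates cannot fail a burdensome test. The documents do not support that. Withdrawal is decided per participant, over the whole schedule, while the gate is per test. Completers can skip one test often enough to take it below 80%, or rate it 3 or lower.

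A reader might treat the acceptance bias as established. It is an inference. Section 7.4 also lists withdrawal reasons that imply no dislike of the App, such as losing the smartphone, visual loss or using PEAK.

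It is tempting to call 8.6 and 9.2.5 a flat contradiction of 11.4.1. They say that withdrawn data enter the analysis but not that it is the primary one, and the planned sensitivity analysis could satisfy them. The intention-to-treat label still does not sit clearly beside a per-protocol primary analysis.

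Two limits on the remedy also stand. Counting a challenge removed for safety as missed would measure applicability rather than adherence. Giving every missing rating the lowest score would penalise tests for unrelated withdrawals: 30 completers at 3.4 and 6 at 1 give (102 + 6)/36 = 3.0, a fail.

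Section 11.5 plans multiple imputation and a complete-case analysis. This does not settle the matter, because a repetition not done is the event being counted, and 11.5 does not say how imputation bears on adherence.

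**Conclusion.** The point holds for adherence. Withdrawal for sustained non-adherence, replacement, and a completer-only deciding set together push the figure upward, because the reason for removal is the quantity being gated. For acceptance, the same direction is probable but depends on withdrawn participants rating tests lower than completers.

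The size cannot be derived from the protocol. Under the assumed rates, between 2 and 16 withdrawals per 30 completers would be needed to reverse a pass on adherence. With few withdrawals the effect may be nil: the illustration with 3 withdrawn still passes, at exactly 80.0%. It should be fixed, since with 30 completers a handful of withdrawals can decide whether a test goes forward. It does not invalidate the study: a planned sensitivity analysis covers all eligible subjects, and selected tests go on to a separate validation study.

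**What to change.** - **Adherence (11.4.1, Step 2 of 11.4.2).** Make all enrolled participants, including those withdrawn and replaced, the primary set. Use each participant's planned repetitions as the denominator and count repetitions after withdrawal as not completed. Keep completers as the sensitivity set. Completers may remain primary for ICC and CV.
- **Removed challenges.** Report those deleted by the nurse as a separate category for each test.
- **Acceptance.** Offer the rated feedback questionnaire to withdrawn participants at the interview already planned, and include their ratings in the acceptance mean. Show lowest-score imputation of missing ratings only as a worst-case bound.
- **Consistency.** Reconcile 8.6, 9.2.5 and 11.4.1 so that each says which population governs which step.

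The withdrawal and safety rules stay as they are. The cost is a change of wording, a short extra questionnaire for those who withdraw, and somewhat less favourable adherence figures. Part of that fall will reflect withdrawals unrelated to test burden; the completer figure beside it shows how much of the difference comes from withdrawn participants. Data up to withdrawal are already kept and the all-eligible analysis is already planned, so for adherence the two sets mainly exchange roles.

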| Statistical Considerations: | 
The sample size was estimated based on published results of similar research in the field (Midaglia et al., J Med Internet Res. 2019). All subjects who complete the study will be included in the primary analysis (per protocol analysis).
 
Primary analyses:
 
The active tests will be selected using a stepwise selection strategy. In step 1, the test reliability will be examined with intra-class-correlation (ICC) and median coefficient of variance (CV). In step 2, user acceptance and adherence will be determined: Feedback on user acceptance will be captured with a feedback questionnaire and a semi-structured interview in week 6. Adherence will be calculated as percentage of completed repetitions divided by the total number of scheduled repetitions for each test. In step 3, all tests that fulfil the minimal requirements for reliability in either ICC or CV, as well as user acceptance and adherence, will be ranked according to their performance in steps 1 and 2. Based on this ranking, tests for each domain will be selected to be further analysed in the validation study.
 
Exploratory Analyses:
 
Potential differences between healthy controls and PwMS on a group level will be analysed with appropriate statistical tests, depending on data category and distribution (e.g. Wilcoxon Signed Rank Test). Although the study is not designed to detect statistically significant differences, results may be used in order to inform test selection for the validation study. For vision tests, dexterity and cognitive tests, correlations with established tests (e.g. "Catch-a-cloud" vs. Nine-Hole-Peg test) will be analysed in order to inform test selection for the validation study.
 |

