##### **End of Study Visits (V3)**

- EDSS
- Feedback questionnaire and semi-structured interview.
- The occurrence of any Adverse Event during the study period will be explored.
- The Fitbit Versa 2 Smartwatch will be handed over to the participants.
- The study conclusion will be drawn (study completed by participant according to the protocol)

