### **11.5 Handling of missing data and drop-outs**

Drop-outs will be replaced. Missing data will be handled by multiple imputation. A complete case analysis will be added as a sensitivity analysis.

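### Sections 8.6 and 9.2.5 do not say which analysis takes withdrawn participants' data, and the completers-only primary set can favour tests near a threshold, most clearly the 80% adherence gate

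*Protocol*

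**What the plan says.** The protocol describes the analysis data in several places.

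- Section 11.4.1: "All subjects who completed the study will be included in the primary analysis (per protocol analysis". The synopsis agrees: "All subjects who complete the study will be included in the primary analysis (per protocol analysis".
- Section 11.4.1 then plans a further intention-to-test "analysis comprising all eligible subjects will be performed as a sensitivity analysis".
- Section 8.6, repeated in 9.2.5: "Data from withdrawn participants (drop out) will be included into analysis (intention to treat analysis". Neither section says whether this is the primary or the sensitivity analysis, and the label differs from the one in 11.4.1.
- Section 11.5: "Missing data will be handled by multiple imputation", with a complete-case analysis as sensitivity. It does not say whether the imputation applies to the completer set, the all-eligible set or both.
- Section 8.4: "Non-compliance (sustained non-adherence to completion of the scheduled exercises) will result in withdrawal". Section 7.4 also withdraws for loss of near vision, loss of hand function and inability to follow procedures, among other reasons.
- Section 7.4: "Withdrawn participants (drop-out) will be replaced by an additional participant". It also says that data collected up to withdrawal are kept and used.

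The selection steps stand under Primary Analysis (11.4.2). A test must reach ICC of at least 0.6 or median CV below 20%, and must also have a mean acceptance rating above 3 and adherence of at least 80%. As 11.4.1 is written, all these gates are judged in completers.

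**The concern.** There are two linked problems.

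The first is wording. A reader of 8.6 or 9.2.5 would put withdrawn participants into the analysis. A reader of 11.4.1 or the synopsis would leave them out of the primary one. Section 11.5 does not settle it, because imputing the missing sessions of drop-outs and restricting the set to completers answer the same problem in different ways.

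The second is selection. Some withdrawal reasons are tied to the quantities being gated. Someone who persistently skips exercises is withdrawn under 8.4, replaced under 7.4, and then absent from the set in which 80% adherence is judged. Someone who loses vision or hand function may also perform less steadily. At stake is which tests go forward to the validation study.

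**Working it through.** The protocol gives no drop-out rate, no expected CV or ICC and no formal sample-size calculation, so there is no figure of its own to reproduce. From the protocol come the group size (30), the thresholds (80% adherence, CV below 20%, ICC at least 0.6), the median as the CV summary, and the rule that ICC or CV suffices. Everything else below is assumed.

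**Adherence**

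Take 30 completers with mean adherence a and w withdrawn participants with mean adherence b, all with the same number of scheduled repetitions. Overall adherence is (30a + wb) / (30 + w). With a = 85% and b = 30%:

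- w = 3: (25.5 + 0.9) / 33 = 80.0%, just at the limit
- w = 4: (25.5 + 1.2) / 34 = 78.5%, fail
- w = 8: (25.5 + 2.4) / 38 = 73.4%, fail

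The gate is met when 30a + 0.3w ≥ 0.8(30 + w), that is w ≤ (30a − 24) / 0.5. This allows 3 withdrawn at a = 85%, 6 at 90% and 9 at 95%. Whenever b is below a, leaving out the withdrawn can only raise the figure.

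**Median CV**

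This was simulated with individual CVs lognormal (log-SD 0.35), 30 completers, and 6 withdrawn with a typical CV of 35%. The chance that the median CV is below 20% is:

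| Typical completer CV | Completers only | With 6 withdrawn at 35% |
|---|---|---|
| 19% | 0.74 | 0.37 |
| 17% | 0.98 | 0.85 |
| 15% | about 1.00 | 0.996 |

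At 19%, 3 withdrawn at 35% give 0.56, and 6 withdrawn at 25% give about 0.55. If the withdrawn resemble completers, nothing is lost (about 0.76). The effect is large only when completers already sit close to 20%.

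**ICC**

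ICC = B / (B + W), with B the between-subject and W the within-subject variance. Scale the completers to B = 0.62 and W = 0.38 (ICC 0.62). Let 20% of participants be withdrawn, with twice the within-subject variance.

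- Same mean as completers: W = 0.38 × (0.8 + 0.2 × 2) = 0.456. ICC = 0.62 / 1.076 = 0.576, so a pass becomes a fail.
- Mean shifted by 2 between-subject SDs: B = 0.62 + 0.2 × 0.8 × 4 × 0.62 = 1.017. ICC = 1.017 / 1.473 = 0.690, so the pass is strengthened.

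The direction therefore depends on how the withdrawn differ from completers.

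**Short series**

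Using data up to withdrawal brings in series with few sessions. For normal data, the median ratio of sample SD to true SD is √(median of χ² on n − 1 df / (n − 1)). For n = 2 it is 0.67, and for n = 10 it is 0.96. A true CV of 25% is then typically observed as 0.67 × 25% ≈ 17% with two sessions and 0.96 × 25% ≈ 24% with ten. Raw two-session CVs would push a test towards passing, so the remedy must not simply admit them.

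**The case against.** The strongest reply is that the two parts of the protocol can be read together. Sections 8.6 and 9.2.5 speak of analysis, not of the primary analysis, and 11.4.1 plans an all-eligible sensitivity analysis to which they may point. The synopsis and 11.4.1 agree on the primary set. This stands: a reader might infer that withdrawn data are discarded altogether, and they are not. The conflict is about role and label. It still needs repair, because 8.6 and 9.2.5 use another name and no role, and nothing says what happens to test selection if the two sets disagree.

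A reader might also infer that completers are the steadier performers, so that reliability is overstated throughout. The documents do not support that. Section 7.4 also withdraws for loss of the smartphone, use of PEAK and concomitant disease, which have no evident link to unstable performance. Section 11.4.2 itself notes that ICC runs low in homogeneous groups, so impaired drop-outs may raise it. A test also needs only ICC or CV, so it leaves the reliability gate only if both fail.

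A third tempting inference is that someone with every session who misses V3 is dropped, while someone with few sessions who attends V3 stays. Among the V3 tasks is "The study conclusion will be drawn (study completed by participant according to the protocol", but no section says that a missed V3 makes a non-completer, and 8.4 withdraws for sustained non-adherence. V3 also supplies the acceptance rating, which is a primary outcome.

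Finally, section 6.1 sets the ICC and CV criteria for ten repetitions, which favours a completer set for those two gates. That is a fair argument for reporting completers alongside. It does not apply to adherence, where the people left out are part of what is being measured.

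**Conclusion.** The concern holds as an unresolved role for withdrawn participants' data, combined with a primary set selected on conduct linked to the gates. The clearest consequence is for adherence, where the bias runs one way: under the assumed inputs, four withdrawn participants turn 85% into 78.5%. Median CV can be flattered, but this decides the result only for tests close to 20%. ICC can move in either direction, so no general lean towards reliable can be claimed. All sizes rest on assumed drop-out numbers, adherence and variances, and with few drop-outs, or drop-outs who resemble completers, the two sets would agree. The repair is cheap and affects the study's main decision, so it should be made.

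**What to change.** Align 8.6, 9.2.5, 11.4.1, 11.5 and the synopsis on one rule and one label:

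- Make the already planned all-eligible set, with all sessions up to withdrawal, primary for the reliability and adherence gates. Make completers the sensitivity analysis.
- Compute adherence over all who started, with all scheduled repetitions as the denominator, including those falling after withdrawal.
- Estimate ICC with a mixed model that accepts unequal numbers of sessions.
- For short series, use a model-based or small-sample-corrected within-subject CV, or require more than two sessions. Do not use raw two-session CVs.
- Name the set used for the acceptance rating, say where multiple imputation applies, and say how test selection proceeds if the two sets disagree.

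The cost is a wording change and slightly more analysis work. No new data are needed, because 7.4 already keeps what was collected before withdrawal. The price is somewhat less favourable adherence figures.
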